#### Heat – outdoor and indoor temperatures and humidity (health impact pathway 1)

To evaluate how housing characteristics and microclimatic conditions influence individual heat exposure, we will conduct a descriptive analysis of indoor and outdoor temperature and humidity, with a particular focus on differences between households with and without cool roofs. This analysis will quantify thermal and humidity gradients across housing types and environments, offering insight into how structural factors influence indoor microclimates and outdoor heat stress conditions.

To ensure a comprehensive characterization of environmental exposure, the following components will be examined:
Daily and seasonal temperature fluctuations, enabling the identification of peak heat stress periods across the agricultural calendar.Indoor – outdoor temperature and humidity differentials, stratified by roof type, ventilation characteristics, and other household attributes, to assess how built environments mediate exposure.The influence of humidity, which plays a critical role in perceived heat stress and modulates physiological responses, especially under high ambient temperatures.

These environmental variables will be statistically summarized using measures of central tendency and dispersion (mean, median, standard deviation, interquartile range), and visualized via time series plots, box plots, and heat maps. Stratified comparisons will also be conducted by region, household type, and season to identify spatial and temporal patterns in heat exposure.

Findings from this microclimate analysis will be integrated into the broader analytical framework (see Figure 5 and Table 1), enabling linkage of environmental conditions with outcomes such as physiological strain, labor capacity, and agricultural productivity. This component is essential for informing both the SEM-based mediation models (Section 2.5.1) and the machine learning approaches (Section 2.5.2), providing environmental context for predictive modeling.

In addition, we will assess how natural variability in environmental parameters – including diurnal temperature ranges, humidity shifts, and extreme weather events – contributes to heat stress dynamics. These factors will be included as covariates or interaction terms in regression and SEM models, ensuring that environmental heterogeneity is appropriately accounted for in downstream analyses of heat-related impacts.

#### Work capacity and physiological response (health impact pathway 2)

To further quantify the relationship between heat exposure and farmers’ work capacity, we will apply a combination of regression models and machine learning techniques. These approaches complement the broader analytical framework by enabling the detection of both linear and non-linear associations between environmental conditions and physiological responses.

Key heat exposure variables – indoor and outdoor temperature, humidity, and Wet Bulb Globe Temperature (WBGT) – will be modeled against continuous physiological indicators such as heart rate, activity levels, and sleep patterns. Linear mixed-effects models will be used to account for within-subject variability and repeated measures, with random effects specified at the individual level to capture heterogeneity in exposure and response. These models will incorporate covariates such as socioeconomic status and farming intensity to control for confounding.

Model validation will involve standard diagnostic tools including residual and Q – Q plots to assess normality, and Variance Inflation Factor (VIF) analysis to detect multicollinearity. In parallel, cross-validation and residual error analysis will be employed to test model robustness and predictive accuracy. Sensitivity analyses will explore how natural variations in environmental conditions – particularly fluctuations in temperature and humidity – affect the stability and reliability of the modeled outcomes.

To enhance the physiological assessment of energy expenditure and physical effort, we will deploy the Renkforce GP-102 GPS Logger, which includes an integrated pedometer function. These devices will collect location and movement data every 15 minutes, allowing for the estimation of energy expenditure based on distance traveled, travel speed, terrain changes, and rest intervals.

Time spent in agricultural fields will be georeferenced, with GPS data linked to each participant’s unique ID and merged with socio-demographic characteristics, field boundaries, and movement patterns. This enables a comprehensive analysis of how mobility and environmental exposure interact to shape work capacity.

Additionally, we will analyze morning travel distances between participant households and agricultural plots – both Euclidean (straight-line) and actual walking paths – to estimate variation in daily physical exertion. These spatial metrics will be evaluated in relation to ambient and nighttime temperatures, providing further insights into how environmental stressors influence the following day’s physiological readiness and labor performance.

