A sample size of 63 participants per group is estimated to detect a mean difference of 5 bpm in heart rate with 95% confidence and 80% statistical power. To accommodate potential attrition and inter-individual variability, the H2H study will enroll a total of 210 participants across 25 villages within the HDSS sites during the feasibility phase.

In the Nouna HDSS, the H2H study is nested within a cluster randomized controlled trial (cRCT) evaluating the effectiveness of cool roof coatings as a passive home cooling intervention (DRKS trials registry number DRKS00023207) [46]. Cool roof coatings are designed to reflect solar radiation and exhibit high thermal emittance, thereby reducing indoor temperatures [47].

The cRCT includes 600 households, with 300 households randomly assigned to receive the cool roof intervention and 300 serving as controls. For the H2H study, farmers will be equally sampled from both intervention and control households to ensure balanced exposure conditions. The H2H study does not treat the cool roof intervention as a direct proxy for heat exposure but considers it a potential modifier of recovery following occupational heat stress.

This nested design facilitates the investigation of both direct and indirect heat-related pathways [1]: direct exposure during agricultural work – analyzing physiological responses, work capacity, and productivity; and [2] post-exposure recovery at home, examining whether improved indoor thermal environments enhance recuperation and influence subsequent health and labour outcomes.

While the cool roof cRCT focuses on the effectiveness of home cooling, the H2H study is primarily concerned with occupational heat exposure. Nevertheless, the interaction between workplace heat stress and home-based recovery conditions is a central component in understanding the cumulative effects of heat on health and productivity over time.

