#### Heat (health impact pathway 1)

##### Indoor air temperature and humidity

Indoor air temperature and relative humidity will be recorded at 15-minute intervals using iButton DS1923 hygrochron and SwitchBot Thermometer & Hygrometer sensors. Additionally, to validate these readings, a portable Wet Bulb Globe Temperature (WBGT) device (PCE-WB20SD, Germany) will be deployed in a subset of households. WBGT is primarily used for outdoor environmental heat stress assessments at workplaces; however, in this study, it will serve as a complementary tool to verify indoor heat conditions.

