##### Outdoor weather metrics

The Nouna and Siaya HDSS areas each have five automatic weather stations that have been operational since mid-2020 (as depicted in Figure 4). These stations continuously record meteorological parameters, including:
Air temperatureRainfallWind speed and directionSolar radiation

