### Data analysis

To examine the cascading effects of heat exposure on farmers’ work capacity and its subsequent impact on child nutrition, we will apply a multi-level analytical approach. Descriptive statistics – including measures of central tendency (mean, median) and dispersion (standard deviation, interquartile range) – will be calculated for each variable. Data distribution, outliers, and potential correlations will be visually assessed using histograms, box plots, and scatter plots.

Analyses will be stratified by age and gender to explore subgroup-specific differences in the effects of heat exposure. The analytical framework – detailing variables, data sources, measurement units, and their classification as continuous or categorical – is presented in Table 1. In addition, a Directed Acyclic Graph (DAG) will be constructed to visualize causal relationships and confounding factors affecting work capacity, agricultural productivity, and child nutritional status (see analytical framework: Figure 5 and Table 1).

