#### Nutritional status (health impact pathway 4)

Anthropometric measurements, including weight and height assessments of children under five years of age, will be used to identify those with poor nutritional status. Nutritional classification will follow the World Health Organization (WHO) Child Growth Standards, where chronic undernutrition (stunting) is defined as a height-for-age z-score (HAZ) ≤ −2.0, and acute undernutrition (wasting) as a weight-for-height z-score (WHZ) ≤ −2.0, adjusted for age and sex [50].

To assess the relationship between heat exposure and child nutritional status, chi-square tests will first be used to evaluate unadjusted associations associations between categorical heat exposure levels and the prevalence of stunting and wasting. To estimate the independent effect of heat exposure on child growth outcomes, multivariate logistic regression models will be employed, adjusting for potential confounders such as household socioeconomic status, dietary intake, and recent illness episodes. To ensure the robustness of these findings, sensitivity analyses will be conducted to control for key confounding factors, including household socioeconomic status, dietary intake, and recent illness episodes. These additional analyses will allow for a more accurate estimation of the independent effect of heat exposure on child growth outcomes, strengthening causal inference within the broader analytical framework.

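### The heat models name no clustering above the individual, and the child models name none, although outdoor heat is measured at five stations per site; the between-person analyses also name no site term

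*Protocol article*

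**What the plan says.** All references are to the protocol article.

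- **Heat and physiology** (Work capacity and physiological response, under Data analysis): linear mixed-effects models "with random effects specified at the individual level to capture heterogeneity in exposure and response". On adjustment: "These models will incorporate covariates such as socioeconomic status and farming intensity to control for confounding". This is an open list. Site, village, station and calendar time are not named.
- **Outdoor exposure** (Outdoor weather metrics): "The Nouna and Siaya HDSS areas each have five automatic weather stations", so ten in total. The article does not say how station readings are assigned to participants.
- **Indoor exposure** (Indoor air temperature and humidity): "Indoor air temperature and relative humidity will be recorded at 15-minute intervals", from indoor sensors.
- **Sample** (Study participants and sample size): "the H2H study will enroll a total of 210 participants across 25 villages within the HDSS sites".
- **Child outcomes** (Nutritional status, under Data analysis): "chi-square tests will first be used to evaluate unadjusted associations", followed by logistic regression with another open confounder list. No random effect, cluster adjustment or site term is named.
- **Levels and strata** (Data analysis): a multi-level approach is announced without naming the levels, and "Analyses will be stratified by age and gender to explore subgroup-specific differences". Region appears as a stratifier only for the environmental descriptives.

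**The concern.** A random effect for the person absorbs stable differences between people. It does not absorb what neighbours have in common on a given day, such as rain, a market day, a shared work calendar or a local outbreak. Outdoor heat is itself common to neighbours on a given day. When exposure and part of the residual are shared by the same group, the model counts more independent information than exists, and its standard error is too small. This affects the model for heart rate, the primary outcome, and the exposure-response functions that the article proposes to pass to climate impact models.

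The child analyses have the same weakness. An ordinary chi-square test or logistic regression treats siblings, any repeat measurements, and children exposed to the same station as independent.

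A second problem applies only where the comparison is between people or places. The two sites differ in climate, disease burden and background undernutrition. If site is left out of a between-person model, a country difference can be read as an effect of heat.

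**Working it through.** **The plan's own figure.** The sample size is 63 per group for 5 bpm, two-sided 5%, 80% power. No SD is stated. With SD 10, n = 2 × (1.96 + 0.84)² × 10² / 5² = 62.7, so 63. The figure is consistent with SD 10, and the formula assumes independent observations with no design effect.

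**Inputs.** From the article: 210 participants, 25 villages, 10 stations, 12 weeks (84 days) per season. Hence 210/25 = 8.4 per village and 210/10 = 21 per station. The 21 assumes an even spread and nearest-station linkage. The size of the shared shock, the autocorrelations and the intraclass correlations (ICCs) are all assumptions; the article gives none.

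**1. Heart-rate model, standard error.** Let s be the share of residual variance that is a station-day shock common to m = 21 farmers.

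- Shocks independent from day to day: variance inflation = 1 + 20s.
- Shock autocorrelation 0.5 and heat autocorrelation 0.6: the shared part is multiplied by (1 + 0.3)/(1 − 0.3) = 1.857, because 0.5 × 0.6 = 0.3. Inflation = (1 − s) + 21 × 1.857 × s.
- True error rate of a nominal 5% test = 2 × [1 − Φ(1.96/√inflation)].

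| s | Inflation, independent | Error rate | Inflation, autocorrelated | Error rate |
|---|---|---|---|---|
| 1% | 1.20 | 7% | 1.38 | 10% |
| 5% | 2.00 | 17% | 2.90 | 25% |
| 10% | 3.00 | 26% | 4.80 | 37% |

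Simulation with 10 stations × 21 farmers × 84 days and no heat effect gives about 6-10%, 15-25% and 25-38%, and about 5% at s = 0.

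A harsher set-up makes 70% of both heat and shock variance common to the whole site, with autocorrelation 0.6 in each. Shocks of 0.7%, 2.7% and 10% of within-person variance then gave rejection rates of 13%, 35% and 57%. With no shock the rate was 6.8% (empirical SE 0.0238, model SE 0.0233).

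**2. Child outcomes.** Design effect DE = 1 + (m − 1) × ICC, with the same error-rate formula.

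| Records sharing exposure | ICC | DE | Error rate |
|---|---|---|---|
| 21 (station-year) | 0.02 | 1.40 | 10% |
| 21 | 0.05 | 2.00 | 17% |
| 63 (21 × 3 rounds) | 0.02 | 2.24 | 19% |
| 63 | 0.05 | 4.10 | 33% |

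The last two rows need heat to be constant at a station over three years, and annual child measurement, which the article does not state.

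**3. Missing site term.**

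- *Heart-rate model.* With no heat effect, an assumed 5 bpm site difference and a 3 °C site gap in heat, the between-person part carries about 0.5% of the weight. The bias is about 0.005 bpm per °C and the test rejects 5.6% of the time. The between-person slope taken alone is about 1.5 bpm per °C and rejects in 98% of runs.
- *Wasting.* The Background gives about 7% in Burkina Faso and 4% in Kenya. The odds ratio is (0.07/0.93)/(0.04/0.96) = 1.81. Spread over an assumed site gap of 2, 3 or 4 °C, that is 1.81^(1/2) = 1.34, 1.81^(1/3) = 1.22 or 1.81^(1/4) = 1.16 per °C. Simulating a pooled logistic model with no heat effect gave odds ratios of about 1.15-1.3 per °C. It rejected in 9-12% of runs with 210 children and 31-36% with 630 child-observations.

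**The case against.** The strongest reply is that this is a condensed article describing a feasibility phase. Its covariate lists are open, it promises a multi-level approach and a causal diagram, and the analysis plan is not shown. Site terms and robust standard errors may well be there. This stands as far as wording goes: the fair statement is that no site term is named, not that none will be used. It does not remove the clustering point. The article chooses a level for the random effects, and it chooses an ordinary chi-square test; both are choices rather than silence.

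Other limits also stand:

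- The inflation is conditional. With no shared variation the individual-level model is about right, and the shock size is assumed.
- Station linkage and the even spread of 21 are inferred.
- Indoor heat is measured by indoor sensors, so the station argument covers outdoor heat only.
- The chi-square test is described as a first, unadjusted step.

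A reader might infer that country differences could create or reverse the heart-rate result. The documents do not support this: heat varies within each person over many days, and nearly all the weight is within person. A reader might also take the odds ratio of 1.81 as the likely bias in wasting. It needs the heat categories to coincide exactly with country and rests on background prevalences. Nor is it true that the article never separates the countries: the yield estimation model is to be adapted to Kenya.

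**Conclusion.** The point holds in a limited form. As written, the mixed models cluster on the individual only and the child models name no clustering. Tests of outdoor heat will therefore reject too often whenever neighbours share outcome variation. A station-day share of 5% is enough to raise a 5% test to about 15-25%, and wider sharing raises it further. For child outcomes 10-17% is the more reasonable range, with 19-33% as the worst case. These sizes rest on assumed shares, ICCs and station linkage.

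Confounding by country is a separate matter. It concerns child nutrition, the comparison of high- and low-yield regions, and the structural equation paths to yield and nutrition, not the within-person heart-rate model.

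**What to change.** - **Mixed models:** add random effects for village and station-day, allowing serial correlation, or use station- or village-clustered standard errors with a small-cluster correction, since there are only ten stations.
- **Child models:** use a mixed or GEE model clustered on household and village or station, and on child if children are measured repeatedly. Keep the chi-square test as descriptive only.
- **Between-person models** (child nutrition, yield regions, structural equation paths to yield and nutrition): include site as a fixed term, or analyse by site and pool.
- **Reporting:** give within-person and between-person heat effects separately.
- **Linkage:** state how station readings are assigned to participants.

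No new data are needed. The cost is wider intervals and, once site is in the model, less exposure contrast in the between-person analyses. Year effects with inference from the within part alone need not be imposed everywhere: they would remove interannual variation that the design sets out to capture.

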Complementing the wearable monitoring, each participant will carry a GPS tracker for a minimum of 20 days annually during the harvest season. The GPS devices will capture spatial and temporal work patterns, including fieldwork duration and distance traveled, offering granular insights into labor exposure under varying thermal conditions. Data from GPS units will be stored locally and synchronized offline by field staff at predefined intervals.

To ensure uninterrupted device operation, participants will be provided with power banks for overnight charging. Additionally, foldable solar panels will be supplied to allow direct charging of devices or recharging of power banks as needed.

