#### Physiological response and work capacity (health impact pathway 2)

To monitor farmers’ physiological responses to heat exposure, the study will deploy two types of wearable devices to enable continuous, high-resolution data collection. All participants will wear the Garmin Vivosmart 5, which records heart rate, step count, and sleep metrics, including duration and quality. This device will be worn throughout the study period to provide real-time data on physiological strain. Additionally, a subset of participants will wear the Activinsights GENEActiv Original, a high-resolution actigraphy device that records gross motor activity and sleep at 10 hz, providing complementary data to the Vivosmart 5. To distinguish between heart rate changes due to physical exertion and those due to heat exposure, the analysis will incorporate methodological corrections, including adjustments for cardiac drift.

To assess work capacity, daily activity, and rest behavior, the study will monitor key indicators such as time engaged in fieldwork, distance traveled, and frequency and duration of rest periods. Each participant will use a Renkforce GP-102 Porter GPS tracker for a minimum of 20 days during the harvest season, capturing spatial and temporal data on labor patterns. GPS data will be stored locally and synchronized offline by field workers at scheduled intervals.

Prior to deployment, compatibility testing will be conducted to ensure that concurrent use of multiple wearable devices does not result in signal interference. Charging logistics will be optimized by providing participants with power banks and foldable solar panels, enabling overnight charging and minimizing disruptions to continuous data collection.

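### Home-to-plot distance suits the night-temperature question poorly: the straight-line version cannot change from day to day, and the walked version mainly records route and plot choice

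*Protocol article*

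**What the plan says.** The data-analysis section on work capacity and physiological response (pathway 2) ends with a spatial analysis. The metric is "morning travel distances between participant households and agricultural plots – both Euclidean (straight-line) and actual walking paths". Its role is "to estimate variation in daily physical exertion. These spatial metrics will be evaluated in relation to ambient and nighttime temperatures". The intended inference is "how environmental stressors influence the following day’s physiological readiness and labor performance".

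Three other places bear on this:
- The same section states the GPS resolution: "These devices will collect location and movement data every 15 minutes". Under study procedures, "each participant will carry a GPS tracker for a minimum of 20 days annually during the harvest season".
- The measurement section for pathway 2 lists work indicators that do vary by day: "time engaged in fieldwork, distance traveled, and frequency and duration of rest periods".
- The section on participants and sample size sets the wider recovery question: "examining whether improved indoor thermal environments enhance recuperation and influence subsequent health and labour outcomes".

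The article does not say how many plots a farmer has. It also does not say whether the distance analysis compares a farmer with himself on other days or compares farmers with each other.

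**The concern.** The question is about change from one day to the next: after a hot night, is the farmer less ready to work? The measure set against night temperature is largely a matter of where people live and farm. A farmer who leaves late, walks slowly or comes home early covers the same distance to the same plot. One who stays at home has no morning distance at all, so the strongest possible response drops out of the data.

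Two misreadings could follow. A flat result might be taken as evidence that hot nights do not affect the next day's work, when the measure could not have shown it. A non-flat result pooled over villages and two countries might be taken as a heat effect, when it describes how far people in warmer places live from their fields.

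**Working it through.** **Inputs.** From the article: two distance metrics, one position every 15 minutes, at least 20 GPS days per year, 210 participants. The article gives no expected effect or precision for this analysis, so there is no figure to reproduce. Number of plots, distances, route variation, walking speed and the true heat effect are assumptions.

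**Step 1: what a slope on distance can contain.** Let d_ij be the distance and T_ij the previous night's temperature for farmer i on day j, with farmer means d̄_i and T̄_i.

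- Within-farmer slope: b_W = Σ(T_ij − T̄_i)(d_ij − d̄_i) / Σ(T_ij − T̄_i)².
- Straight-line distance, one plot: d_ij = d̄_i on every day, so the numerator is 0 and b_W = 0 whatever the true effect.
- Pooled slope: (S_W·b_W + S_B·b_B) / (S_W + S_B), where S_W and S_B are the within- and between-farmer sums of squares of T. With b_W = 0, only b_B remains: the relation between a farmer's average distance and average night temperature. That is location, village and site.

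**Step 2: simulation.** 210 farmers, 20 days, 300 runs. Night temperature is a shared daily component (SD 1.5 °C) plus an individual one (SD 1 °C). Plot distances are lognormal with median 2 km (log SD 0.6). The true effect is −0.3 field hours per 1 °C, with SD 1 h between farmers and 1.5 h between days. All slopes are within farmer.

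| Outcome | Share of variance within farmer | Mean slope per 1 °C | Runs rejecting at 5% |
|---|---|---|---|
| Straight-line distance, one plot | 0% | 0 exactly | 0% |
| Walked distance, one plot, 10% random route variation | 3% | 0.00 km | 6% |
| Two plots, choice unrelated to heat | 48% | 0.00 km | 5% |
| Two plots, log-odds of choosing the nearer rise by 0.3 per 1 °C | 48% | −0.11 km | 100% |
| Hours in the field | 69% | −0.30 h | 100% |

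Rows 2 and 3 reject at about the nominal rate. In row 4 distance does respond, but what it shows is the change of destination that was built in.

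**Step 3: resolution of the walked path.** Spacing between positions = speed × 0.25 h: 0.75 km at 3 km/h, 1.0 km at 4 km/h, 1.25 km at 5 km/h. Expected positions on a walk of D km at 4 km/h = (D/4 × 60)/15 = D. A 1 km walk gives about one position and a 0.5 km walk about half of one. For short walks the recorded path adds little to the straight line. This loss is not included in row 2.

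**The case against.** The strongest reply has five parts.

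1. **Only the straight-line metric is fixed.** The article also names walked paths, and its ethics section speaks of a participant's fields in the plural. This stands. A reader might infer that distance as a whole is fixed and can show nothing; the text does not support that, and row 4 of the table shows distance responding when plot choice depends on heat.
2. **Going to a nearer plot after a hot night is itself a result.** Hypothesis 2 expects heat to alter farming behaviour. This also stands, and it is a reason to report such a change as behaviour. It does not make it a measure of readiness, because distance alone cannot separate fatigue from which plot needed work.
3. **Other analyses touch on recovery.** A reader might infer that this is the only link between night heat and later work, so that the study would wrongly conclude hot nights do not matter. The documents do not support that. The section on advanced methods plans recurrent networks for lagged effects using indoor temperature and work/rest cycles. The pathway 2 section plans mixed models of indoor temperature against heart rate, activity and sleep. Farmers are also sampled equally from cool-roof and control households. None of these, however, states a model of the previous night's temperature against next-day labour.
4. **The wording does not call distance the outcome**, and an article may leave model form to the full plan. This is fair. But if distance is meant as a load variable, the passage names no outcome for the inference it draws.
5. **The simulation with heat-independent plot choice builds in a null slope.** True. Row 3 shows only that day-to-day variation in distance need not carry readiness. The claim for straight-line distance rests on step 1, not on simulation.

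**Conclusion.** The point holds in limited form. For a given house and plot, straight-line distance carries no information on the effect of the previous night: its within-farmer slope is 0 by construction. Walked distance and destination can vary, but mainly reflect route and plot choice, and short walks are poorly resolved at 15-minute intervals. An association pooled across farmers would largely describe settlement geography and site.

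The reach is modest. This is a supplementary analysis in a feasibility phase, and the primary outcome, heart rate, is unaffected. The zero slope for straight-line distance to one plot needs no assumption. The other simulated figures depend on assumed plot numbers, distances, route variation and effect size, and the spacing of positions depends on assumed walking speed.

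**What to change.** For the night-temperature question in the pathway 2 analysis section:

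- Use day-varying measures already collected as outcomes: field attendance, departure time, hours in the field, rest periods, activity and heart rate.
- Regress each, within farmer, on the previous night's indoor temperature, with same-day outdoor heat in the model so that a hot night is not confused with the hot day that follows.
- Keep home-to-plot distance as a covariate for that day's travel load.
- Report any change in walked distance or choice of plot as farming behaviour, not as readiness.

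The cost is wording and analysis code; the GPS, wearable and indoor-sensor data are those already planned. Two practical limits should be stated. GPS-based measures exist only for the days the tracker is carried, and departure time is known only to about 15 minutes. Because consent covers wearing the GPS device during work activities, the plan should also say how a day without fieldwork is told apart from a day without a tracker.
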